## Abstract

**Background:**

Diabetic macular edema (DME) is the main cause of vision loss in diabetic patients. Currently, anti-vascular endothelial growth factor (VEGF) intravitreal injection stands as the first-line therapy for DME. However, some patients exhibit insufficient response to anti-VEGF agents and often require multiple injections, imposing psychological and economic burdens. While microinvasive pars plana vitrectomy (PPV) has been shown to be safe and effective in treating refractory DME, scant research has explored its application to treatment-naïve DME. The purpose of this study is to determine whether early PPV combined with internal limiting membrane (ILM) peeling can lessen the therapeutic burden of DME patients, prevent vision loss, and maintain long-term stabilization of diabetic retinopathy.

**Methods:**

This is a single-center, prospective, parallel-group, non-inferiority randomized controlled trial involving 102 DME participants. Participants will be randomly assigned to either the study group (PPV combined with ILM peeling) or the control group (conbercept intravitreal injection (IVC)) at a 1:1 ratio, with a scheduled follow-up at 12 months post-operation. Comparative analysis of results between the two groups will be conducted at months 1, 3, 6, and 12 after the intervention. The primary outcomes involve evaluating the changes in central subfield thickness (CST) and best corrected visual acuity (BCVA). The secondary outcomes include assessment of optical coherence tomography (OCT) and OCT angiography (OCTA) biomarkers, re-treatment and adverse events rates, diabetic retinopathy (DR) development, cost-effectiveness analysis, and vision-related quality of life (VRQL).

**Discussion:**

Some patients do not respond well to anti-VEGF drugs and repeated intravitreal injections increase the treatment burden for patients. The VVV study aims to explore whether PPV combined with ILM peeling could become an initial treatment option for treatment-naïve DME patients.

**Trial registration:**

ClinicalTrials.gov NCT05728476. Registered on 15 February 2023.

## Administrative information

Note: the numbers in curly brackets in this protocol refer to SPIRIT checklist item numbers. The order of the items has been modified to group similar items (see http://www.equator-network.org/reporting-guidelines/spirit-2013-statement-defining-standard-protocol-items-for-clinical-trials/).

## Introduction

### Background and rationale {6a}

Diabetic macular edema (DME), characterized by the accumulation of exudative fluid in the macula, is the leading cause of vision loss in diabetic patients [1]. With optical coherence tomography (OCT), approximately 5.47% of diabetic patients can be diagnosed with DME [2]. Given the rising prevalence of diabetes [3], DME is becoming an increasingly significant public health concern.

Although the pathogenesis of DME remains unclear, over-expression of vascular endothelial growth factor (VEGF) and over-release of inflammatory cytokines are associated with DME according to recent studies [4]. Focal/grid laser treatment was formerly the gold standard for treating DME, but it could only reduce the chance of moderate vision loss and most patients could not regain lost vision after undergoing this procedure [5]. In contrast, vitreous injection of anti-VEGF has demonstrated greater effectiveness and has become the first-line therapy in treating DME [6]. Conbercept is a 141-kDa engineered fusion protein that has a high affinity for binding all isoforms of VEGF-A, VEGF-B, VEGF-C, and PIGF [7]. Single conbercept intravitreal injection (IVC) can reduce ocular VEGF concentration for more than 60 days [8]. Previous studies have shown the effectiveness and safety of IVC in DME treatment [9–11]. However, a considerable proportion of patients do not react effectively to anti-VEGF agents and often require multiple injections [12]. Refractory or persistent DME refers to eyes that have undergone 4 anti-VEGF injections within 6 months and have a persistent central subfield thickness (CST) of 250 μm or more on OCT scans, as determined by the Diabetic Retinopathy Clinical Research Network (DRCR.net) [13]. After 2 years of monthly injections, over 40% of patients in DRCR protocol I had refractory DME [14], and at least 26% patients in RISE/RIDE study had the same issue [15]. Obviously, refractory DME is not uncommon and typically requires additional treatment, elevating the psychological and economic burden of patients [16]. In addition, repeated injections may lead to degeneration of the remaining healthy retinal nerves, increasing the risk of choroidal capillary circulatory disturbance [17]. As a result, there is a great demand for alternative therapy that can effectively manage DME with lower treatment burden.

Lewis et al. firstly reported pars plana vitrectomy (PPV) as a therapy for tractional DME in 1992 [18]. Microinvasive vitreous surgery and an optimized vitrectomy platform with fluid and pressure control have greatly reduced the complications of PPV, resulting in a relatively low complication rate of approximately 1%, which is similar to the cumulative and serious complication rate associated with repeated anti-VEGF injections [19, 20]. The possible mechanisms of PPV for DME include relieving the mechanical traction of macula, increasing the oxygenation within the vitreous cavity, and promoting the clearance of VEGF [21–25]. PPV is currently proposed when traditional therapies fail in treating refractory DME cases that are accompanied by posterior vitreous cortical retraction, hard exudates in the fundus, and vitreous macular traction [26–28]. When combined with ILM peeling, PPV can release mechanical traction, completely remove the residual posterior vitreous cortex that cannot be cleared by traditional PPV, and prevent the formation of epiretinal membrane [29]. In addition, PPV combined with ILM peeling can reduce the attachment of vasoactive and inflammatory factors, leading to a lower incidence of vitreoretinal interface disease postoperatively [30–33]. Studies have shown that PPV combined with ILM peeling is safe and efficient for both tractional and non-tractional DME [30, 34–36]. However, in previous studies, PPV was mostly considered to be a last resort for DME. Due to failed treatments and a long course of the disease, the photoreceptors as well as the outer membrane have been damaged, thus limiting the therapeutic effect [37–39].

OCT and OCT angiography (OCTA) have become essential techniques in identifying biomarkers for DME, which have been demonstrated to be closely correlated with therapeutic efficacy. Many studies have demonstrated the correlation between various imaging biomarkers and the response to anti-VEGF drug treatment, including subretinal fluid (SRF), location and size of cystoid change, continuity of the inner segment-outer segment (IS-OS) layer, hyperreflective foci (HRF), and the status of the vitreomacular interface in OCT [40–42], as well as the foveal avascular zone (FAZ) and retinal blood flow density in OCTA [43–45]. Nevertheless, there exists a paucity of examining imaging biomarkers in treatment-naïve DME patients undergoing vitrectomy. And only the VITAL study has identified the presence of SRF as a predictive anatomical factor for better visual outcomes [36]. Therefore, our study aims to further explore which biomarkers are more suitable for surgical treatment compared to anti-VEGF drug treatment.

### Objectives {7}

#### Main objective

The main objective is to compare the changes in best corrected visual acuity (BCVA) and CST in patients with treatment- naïve DME who undergo PPV combined with ILM peeling versus those who receive conbercept intravitreal injection.

#### Secondary objectives

The secondary objectives include assessment of OCT and OCTA biomarkers, diabetic retinopathy (DR) development, re-treatment, adverse events, cost-effectiveness analysis, and vision-related quality of life (VRQL) of the two groups.

### Trial design {8}

VVV is a single-center, prospective, parallel-group, non-inferiority, randomized controlled trial. Enrolled patients will be randomly assigned at a 1:1 ratio into the study group (PPV combined with ILM peeling) and control group (IVC), and a follow-up period of 12 months is planned. Interim analyses will not be conducted. Figure 1 depicts the trial design flow chart.

**Fig. 1 Fig1:**
[figure not shown]
Trial design flow chart. DME, diabetic macular edema; PPV, pars plana vitrectomy; ILM, internal limiting membrane; d, day; w, week; m, month

## Methods: participants, interventions, and outcomes

### Study setting {9}

This study will be carried out during November 1, 2023, to November 1, 2025, at Tianjin Medical University Eye Hospital in Tianjin, China. The hospital is a class A tertiary hospital specializing in the treatment of eye diseases and provides services to patients from Tianjin and the surrounding areas. The recruitment, surgery, and follow-up will all take place here. A dedicated investigator will communicate with patients who are eligible for our inclusion about the specifics of the trial. Before undergoing any interventions related to this research, each participant must sign an informed consent form. Researchers will present the trail in popular expression to ensure that participants can fully understand the benefits as well as potential harms and participate voluntarily. Participants can withdraw from the study whenever they choose for any reason.

### Eligibility criteria {10}

The following are the criteria for the inclusion of candidates: (1) ≥ 18 years of age; (2) patients and their families fully understand the research and must sign an informed consent form; (3) diagnosed with type 1 or 2 diabetes mellitus; (4) hemoglobin A1c (HbA1c) levels of < 10% within 3 months; (5) moderate or severe nonproliferative diabetic retinopathy (NPDR) and proliferative diabetic retinopathy (PDR) without vitreous/preretinal hemorrhage [33]; (6) clear media for adequate OCT and OCTA images; (7) treatment-naïve DME diagnosed clinically; (8) CST of > 300 μm; (9) Early Treatment Diabetic Retinopathy Study (ETDRS) BCVA between 24 and 73 letters on the day of randomization; (10) treatment within 12 months of DME diagnosis; (11) no contraindication of vitrectomy or conbercept intravitreal injection. Each participant will only have one eye examined. If both eyes are qualified, the researcher will decide which of the eyes will be included in this study.

Exclusion criteria include the following: (1) any previous DME treatment (i.e., anti-VEGF injections, intravitreal corticosteroid usage, or macular photocoagulation); (2) macular edema caused by other diseases (i.e., age-related macular degeneration, retinal vein occlusion); (3) any previous intraocular surgeries (cataract surgery performed at least three months before study entry will not be exclusionary); (4) vision loss caused by other ocular diseases (i.e., glaucoma, high myopia); (5) a follow-up duration of < 12 months; (6) severe dysfunction of the heart, liver, kidney, lung, or other organs.

### Who will take informed consent? {26a}

Prior to involvement in this study, the principal investigator and delegated sub-investigators will provide potential participants with detailed information about the purpose, procedures, risks, and benefits of the research. Participants will have the opportunity to ask questions and clarify any concerns they may have. Only after receiving this information and providing voluntary consent will individuals be included in the study.

### Additional consent provisions for collection and use of participant data and biological specimens {26b}

Not applicable. There will be no additional consent provisions, and this study will not involve biological specimens.

## Interventions

### Intervention description {11a}

#### Control group

Patients will undergo three intravitreal injections of 0.5 mg conbercept (Chengdu Kanghong Biotech Co., Chengdu, China) per month with a 30-guage syringe needle 3.5–4 mm posterior to the corneal limbus under topical anesthesia [46].

#### Study group

Standard 25-guage PPV will be performed under retrobulbar anesthesia using Constellation vitrectomy system (Alcon. Laboratories, Inc., Fort Worth, TX). Phacoemulsification and intraocular lens implantation will be performed for cataract affecting vision. After the central vitreous is removed, the surgeon will make a complete posterior vitreous detachment to clear the attached posterior hyaloid. The ILM stained with indocyanine green will be peeled up to the vascular arcades. Pan-retinal photocoagulation (PRP) can be performed during surgery if needed. In the end, the vitreous cavity will be filled with balanced salt solution. An experienced surgeon will complete all the surgical procedures.

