### Further intervention

Thereafter, each participant will receive pro re nata (PRN) conbercept therapy, with regular monitoring for 12 months, at least 1 month apart for the vitrectomy of the study group and 3 months apart for the first intravitreal injection of the control group. PRN conbercept treatment will be performed if the following criteria are met: (1) existence of recent or persisting cystoid retinal lesions, (2) a decrease of no less than 5 ETDRS letters in BCVA, and (3) an increase of 50 μm or more in CST compared with the best value previously achieved. If high-risk PDR without definite vitreous or preretinal hemorrhage or severe NPDR with high-risk characteristics and reduced visual acuity are present, PRP treatment will be administered. Cataract surgery will also be allowed for cataract that affect vision. PPV will be performed if there exist un-clearing vitreous hemorrhage (1–6 months) and/or tractional retinal detachment. Patients with postoperative ocular hypertension will first receive drug treatment to lower their intraocular pressure. If medication is unable to control persistent high intraocular pressure, they will undergo anti-glaucoma surgery. Other further interventions will be conducted based on the specific circumstances.

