### Outcomes {12}

#### Primary outcome

The primary outcome is the changes in BCVA and CST from baseline to month 12 between the two groups.

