### Sample size {14}

The sample size is estimated by the change of BCVA using PASS 15.0 (PASS 15.0.5 NCSS, LLC, USA). According to a published paper [9], mean BCVA change of IVC from baseline to month 12 was 8.2 ± 9.5 ETDRS letters. The maximum difference of 5 ETDRS letters was chosen for non-inferiority margin between groups. The sample size was calculated based on α level of 0.05 and *β* level of 0.2, N1 = N2 = 46. Then, the ultimate sample size is 102 (51 of each group) assuming a 10% dropout rate.

The non-inferiority margin was chosen because 5 ETDRS letters is considered clinical insignificant in practice. And the sample size is also sufficient for analysis of the change of CST based on previous studies [9, 36] (364 ± 88.6 μm and 200 ± 210 μm for IVC and vitrectomy combined with ILM peeling respectively).

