## Discussion

The high incidence of refractory persistent DME necessitates the research for a more efficacious method for treating DME. Based on previous studies [30, 34–36], we have ample reasons to postulate that PPV is safe and effective for treatment-naïve DME. Moreover, PRP and cataract surgery can be performed simultaneously with PPV, obviating the need for continual hospital visits for treatment. However, PPV has mostly been used to treat refractory DME before, and the long-term course of disease and repeated intravitreal injections may have caused irreversible damage to the retina. Hence, we are going to explore whether early PPV combined with ILM peeling can reduce the therapeutic burden of DME patients, prevent vision loss, and maintain long-term stabilization of diabetic retinopathy, thus becoming as an initial therapy choice for treatment-naïve DME patients. Furthermore, with the assistance of OCT and OCTA, we will assess the imaging biomarkers connected with surgical treatment effectiveness.

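### Vision-affecting cataract is removed at the index operation in the PPV arm but only as a later option in control eyes, so the month-12 BCVA difference compares strategies that include lens surgery and does not by itself isolate PPV with ILM peeling

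*Protocol article*

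**What the plan says.** - **PPV arm.** The Study group text under Intervention description {11a} puts lens removal inside the index operation, in mandatory wording: "Phacoemulsification and intraocular lens implantation will be performed for cataract affecting vision".
- **Control arm.** The Control group text gives three conbercept injections and no lens surgery.
- **Both arms, later.** Further intervention, which applies to every participant after the initial treatment, is permissive: "Cataract surgery will also be allowed for cataract that affect vision".
- **Objective.** The main objective compares BCVA and CST changes in patients "who undergo PPV combined with ILM peeling versus those who receive conbercept intravitreal injection". Lens surgery is not mentioned.
- **Discussion.** Combined surgery is presented as an advantage: "PRP and cataract surgery can be performed simultaneously with PPV, obviating the need for continual hospital visits for treatment".
- **Endpoint and margin.** "The primary outcome is the changes in BCVA and CST from baseline to month 12 between the two groups". For BCVA, "The maximum difference of 5 ETDRS letters was chosen for non-inferiority margin between groups".
- **Eligibility {10}.** Inclusion 6 asks for "clear media for adequate OCT and OCTA images". Exclusion 4 bars "vision loss caused by other ocular diseases (i.e., glaucoma, high myopia"). Cataract is not among its examples.
- **Other provisions.** Progression of cataract is a safety item. Participants and surgeons are not blinded ({17b}). Adjusted regression is planned in general terms ({20b}).

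**The concern.** A lens opacity lowers BCVA whatever the state of the macula. Under the text as written, the same baseline cataract is removed at T0 if the eye is allocated to PPV. If it is allocated to control, the cataract is removed later or not at all, by a separate decision taken by unblinded clinicians. One arm's treatment package therefore contains a possible source of BCVA gain that has nothing to do with the vitreous or the ILM.

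What is at stake is how the BCVA result is read. A non-inferior result could owe something to lens replacement. A failed one could owe something to cataract developing in vitrectomised eyes that kept their own lens. The planned BCVA comparison cannot tell these from the contribution of PPV with ILM peeling. If lens status is not recorded before T0, it is hard to recover reliably once the lens has been removed.

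**Working it through.** **1. The texts side by side.**

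| | PPV arm | Control arm |
|---|---|---|
| Initial treatment | PPV with ILM peeling, plus lens surgery if cataract affects vision (mandatory wording) | Three conbercept injections |
| After initial treatment | Cataract surgery permitted if cataract affects vision | Cataract surgery permitted if cataract affects vision |

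The trigger is nearly the same in both arms. Timing and obligation differ.

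**2. Do existing provisions remove the asymmetry?**
- Inclusion 6 limits dense cataract, but its standard is image quality. The lens-surgery clause in the Study group text itself expects some enrolled eyes to have cataract that affects vision.
- Exclusion 4 could be read to cover cataract, but it does not say so. If it did, the lens-surgery clause would have little use at T0.
- Masked assessment ({17a}) protects measurement, not treatment content.
- Regression on baseline factors can improve precision. It cannot separate lens surgery that is delivered as part of one arm's treatment.

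**3. Can the size be fixed?** Contribution to the BCVA difference = d × g, where d is the net difference between arms in the share of lens-affected eyes at month 12 and g is the mean letter effect per such eye. The document gives neither. By assumption only:
- d = 0 (surgery matched by month 12): 0 letters.
- d = 0.15, g = 7.5: 0.15 × 7.5 = 1.1 letters.
- d = 0.50, g = 15: 0.50 × 15 = 7.5 letters.

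The sign is open too. Lens removal at T0 may favour PPV, and later cataract in phakic vitrectomised eyes may work against it. A range this wide, with no sign, shows only that the document does not settle the matter. I therefore attach no error rate or loss of power to it.

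**4. The plan's own figure.** Inputs from Sample size {14}: SD 9.5, margin 5, α 0.05, β 0.2, 46 per arm. I take the true difference as 0.
- SE = 9.5 × √(2/46) = 1.981.
- Noncentrality = 5/1.981 = 2.52, with 90 degrees of freedom.
- Power at one-sided 0.05 = 80.5%; 45 per arm gives 79.7%. The stated 46 is reproduced.
- 90% interval half-width = 1.662 × 1.981 = 3.29 letters.

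**5. Precision of a subset analysis** in eyes without vision-affecting cataract at baseline. The share left out is assumed, and n is rounded down from 46. Half-width = t(0.95, 2n − 2) × 9.5 × √(2/n).

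| Left out | n per arm | 90% half-width (letters) | Power at true difference 0, one-sided 0.05 |
|---|---|---|---|
| 0% | 46 | 3.29 | 80.5% |
| 10% | 41 | 3.49 | 76.4% |
| 20% | 36 | 3.73 | 71.4% |
| 30% | 32 | 3.97 | 66.9% |
| 40% | 27 | 4.33 | 60.4% |

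**The case against.** The strongest reply is that nothing here is an error. Randomisation makes the comparison of the two strategies valid. The Discussion frames PPV as a candidate initial therapy and openly counts combined cataract surgery among its benefits. Control eyes may have the same surgery within the 12 months, and the eligibility criteria already limit cataract. CST, the other primary outcome, gives an anatomical measure of the edema beside BCVA. Lens-status fields, covariates and subset analyses are also details that an article often leaves to the full protocol or SAP.

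Most of this stands.
- The strategy comparison is unbiased, and its primary analysis should not change.
- A reader might infer that the protocol claims to estimate the effect of PPV on DME. It does not: the main objective compares outcome changes in patients who receive each treatment.
- A reader might also infer that CST is distorted. Nothing in the document shows that.
- The absence of a named covariate or subset is not itself the point.

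What does not fall away is the mismatch between provisions that the article does state. The Study group text builds lens surgery into one arm's index treatment, and the main objective names only PPV with ILM peeling. CST does not divide a BCVA difference into its sources, and later surgery in controls is permitted rather than assured.

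**Conclusion.** The point holds as a matter of interpretation and as a cheap improvement. The month-12 BCVA difference compares PPV with ILM peeling, plus lens surgery when needed, against conbercept with optional later lens surgery. It does not by itself isolate PPV with ILM peeling.

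For the strategy question the bias is zero. For the narrower reading, neither the size nor the direction can be fixed from the document. The contribution would be near zero if control eyes had matching surgery before month 12, or if exclusion 4 keeps out vision-affecting cataract.

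It is tempting to say that the design favours PPV or inflates the chance of declaring non-inferiority. The document does not support that, because it gives no cataract share, no letter effect and no net sign.

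**What to change.** 1. Keep the primary analysis, and state in the objective and intervention text that the PPV strategy includes lens surgery when cataract affects vision.
2. State whether exclusion 4 covers cataract.
3. Record lens status before allocation, at the screening eye examination already in the schedule: pseudophakic, clear, or cataract affecting vision.
4. Use that baseline status as a covariate, for precision.
5. Pre-specify one supportive sensitivity analysis of month-12 BCVA change in eyes without vision-affecting cataract at baseline. The subset is fixed before randomisation, so it does not condition on later surgery.
6. Report cataract surgery at T0 and to month 12 by arm, beside the BCVA result.

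**Cost.** One baseline field and some wording. The article states that recruitment had not begun. The subset loses precision: with 10–40% of eyes left out, 41 to 27 per arm remain and the 90% half-width grows from 3.3 to 3.5–4.3 letters. Later cataract in phakic vitrectomised eyes may tilt it against PPV. It should be labelled supportive and cannot replace the primary result.
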